## Abstract

Photobiomodulation is a safe option for controlling pain, edema, and trismus when applied postoperatively in third molar surgery. However, administration prior to surgery has been under-explored. This study aims to explore the effectiveness of pre-emptive photobiomodulation in reducing postoperative edema in impacted lower third molar extractions. Two groups of healthy individuals undergoing tooth extraction will be randomly assigned: Control group receiving pre-emptive corticosteroid and simulated photobiomodulation, and Photobiomodulation Group receiving intraoral low-intensity laser and extraoral LED cluster application. The primary outcome will be postoperative edema after 48 h. The secondary outcomes will be pain, trismus dysphagia, and analgesic intake (paracetamol). These outcomes will be assessed at baseline as well as two and seven days after surgery. Adverse effects will be recorded. Data will be presented as means ± SD and a p-value < 0.05 will be indicative of statistical significance.

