### Sample size calculation

The sample size was calculated to provide an 80% power (α = 0.05). The sample size will consist of 30 surgeries per group. Thirty patients with bilateral and symmetric lower third molars (right and left) will be selected. The procedure will then be performed randomly (split-mouth design), totaling 60 surgeries (30 surgeries in the control group and 30 surgeries in the experimental group). For the calculation, we used the 48-hour time point in the article by Aras and Güngörmüş (2010) [21]. The average edema measurement was 105 mm in the control group and 109 mm in the experimental group. The larger standard deviation between the two means ±5 mm was chosen for the sample size calculation.

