### Study outcomes

The primary outcome of the study will be:

Edema—three measurements will be taken on the patient’s face with a previously sanitized flexible measuring tape: tragus-pogonion, tragus-labial commissure, and mandibular angle-outer orbital commissure [26]. Measurements will be taken immediately before surgery as well as two and seven days after surgery.

The secondary outcomes of the study will be:

Pain Sensitivity*—*The visual analog scale (VAS) is the most widely used instrument for measuring postoperative pain after oral surgeries with photobiomodulation in the postoperative period [24, 26]. In this study, the VAS will be used immediately after surgery as well as two and seven days after surgery [24, 26] using 10-cm line with "0" (no pain) at one end and "10" (unbearable pain) at the other. Instructions on marking will be provided to the patient by the same operator.

Quantity of pain tablets taken during the period*—*The number of analgesic tablets taken at two and seven days will be counted. All participants will take paracetamol and be instructed to take it every six hours only in the presence of pain [27]. At the beginning of the study, each participant will be provided a paracetamol tablet, which is a drug with purely analgesic effects [28]. At the end of the experiment, the quantity of tablets will be evaluated as a secondary outcome. Patient adherence will be monitored. For such, the patients will be asked to bring the medication blister pack to the appointment to check how it is being used.

Postoperative trismus assessment*—*Spasms in the masticatory muscles (trismus) can limit or even prevent mouth opening after the surgical removal of impacted third molars [21, 23, 29]. This outcome is typically evaluated by measuring the distance between the incisal edges of the upper and lower central incisors using calipers [27, 29]. In this study, previously calibrated evaluators will measure mouth opening in each patient before surgery as well as two and seven days after surgery.

Impact of the surgical procedure on quality of life*—*Two previously calibrated evaluators will ask patients to respond with "yes" or "no" to the following 10 questions two and seven days after surgery, as described by Sierra et al. (2013) [26] and Sierra et al. (2015) [24].

The 10 questions were:

Are you maintaining your social activities normally?

Are you working/studying normally?

Are you maintaining your regular diet?

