### Statistical analyses

Initial descriptive analyses will be performed for all variables measured in the study, both quantitative (mean and standard deviation) and qualitative (frequencies and percentages). Normality tests will then be conducted to determine the appropriate statistical tests for specific analysis. Subgroup analysis will be performed: treatment x sex interaction [31]. A significance level of 5% probability or corresponding p-value will be adopted for all tests. All analyses will be conducted using the statistical software SPSS for Windows, version 9.1. Interim analysis was not planned.

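### The primary outcome is three facial distances with no single primary quantity; if each were tested at 5% and any one counted, the false positive chance would be about 7% to 14%

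*Protocol article*

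**What the plan says.** Four places in the protocol article bear on the primary quantity.

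- **Study outcomes.** For the primary outcome, edema, "three measurements will be taken on the patient’s face with a previously sanitized flexible measuring tape": "tragus-pogonion, tragus-labial commissure, and mandibular angle-outer orbital commissure". On timing, "Measurements will be taken immediately before surgery as well as two and seven days after surgery". No sum, mean, change score or lead distance is given.
- **Abstract.** "The primary outcome will be postoperative edema after 48 h". This fixes the time but not the quantity.
- **Statistical analyses.** "A significance level of 5% probability or corresponding p-value will be adopted for all tests". No multiplicity adjustment is mentioned, and no test is named for edema.
- **Sample size calculation.** The figures come from the 48-hour results of one cited study: "The average edema measurement was 105 mm in the control group and 109 mm in the experimental group", and "The larger standard deviation between the two means ±5 mm was chosen for the sample size calculation". With 80% power and alpha 0.05, the article states 30 surgeries per group in 30 split-mouth patients. It does not say which distance, or what combination of distances, the 105 and 109 mm describe.

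**The concern.** A primary test compares one number between the two sides of the mouth. Here the reader cannot tell which number. With three distances listed as primary and an unadjusted 5% for all tests, the text permits three primary tests and does not exclude a claim of reduced edema from whichever line reaches significance.

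Two things are at stake. The 5% error rate may not hold for the trial's main claim. The quantity that was powered may also differ from the quantity that is tested. Blinding the statistician, as the article plans, does not remove the first problem: a line can be chosen once the p-values are known, even while the group labels are still masked.

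**Working it through.** **1. The plan's own figure.** The inputs, from the Sample size calculation section, are a difference of 109 − 105 = 4 mm, SD 5 mm, alpha 0.05 and power 80%. Sidedness is not stated; two-sided is assumed.

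- Two independent groups, normal formula: n = 2 × (1.960 + 0.842)² × 5² / 4² = 2 × 7.85 × 25/16 = 24.5, so 25 per group. The two-sample t-test gives 26.
- Power at 30 per group is 87.3% (normal) or 86.1% (t), not 80%.
- Paired t-test, with SD of differences = 5 × √(2(1 − ρ)) for within-patient correlation ρ: 27 pairs at ρ = 0 (SD 7.07 mm) and 15 pairs at ρ = 0.5 (SD 5 mm).

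These inputs do not give exactly 30; they need fewer. That is a separate matter and does not affect the error rate below. What matters here is that the calculation has room for one quantity only. If 105 mm were a sum of three distances, the lines would average 105/3 = 35 mm. A single line or a mean of lines is the more natural reading, but that is an inference; the article does not say.

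**2. Error rate if the lines are tested separately.** Take three two-sided tests at 5%, at 48 h, with success on any one and no true effect.

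Independent lines: 1 − 0.95³ = 1 − 0.8574 = 14.3%.

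For a common correlation r between the three lines' treatment differences (equicorrelated normal model, c = 1.96):

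error = 1 − ∫ φ(u) × [Φ((c − √r·u)/√(1 − r)) − Φ((−c − √r·u)/√(1 − r))]³ du

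The last column simulates 200,000 trials of 30 pairs with paired t-tests.

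| r | Normal model | Multiple of 5% | Simulated |
|---|---|---|---|
| 0 | 14.3% | 2.9 | 14.2% |
| 0.3 | 13.6% | 2.7 | 13.6% |
| 0.5 | 12.5% | 2.5 | 12.7% |
| 0.7 | 10.9% | 2.2 | 11.0% |
| 0.8 | 9.8% | 2.0 | 10.1% |
| 0.9 | 8.4% | 1.7 | 8.4% |
| 0.95 | 7.3% | 1.5 | not run |

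In the normal model the rate passes 10%, double the stated level, only when r is below about 0.79. The article gives no value for r.

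**3. Error rate with one quantity.** One named line, or one mean or sum of the three at 48 h, tested once, gives 5.0%.

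**4. What averaging does to precision.** With equal variances, the SD of the mean relative to a single line is √((1 + 2r)/3):

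- r = 0.5: √(2/3) = 0.82.
- r = 0.8: √(2.6/3) = 0.93.

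If all three lines carry the same effect, the mean is at least as precise as any one line. If the effect is confined to one line, it is diluted. For example, 4 mm on one line becomes 4/3 = 1.33 mm in the mean. If each line has SD 5 mm and r = 0.5, the standardised effect falls from 4/5 = 0.80 to 1.33/(0.82 × 5) = 0.33.

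**The case against.** The strongest reply is that the article points to one quantity. The Abstract speaks of edema in the singular at one time, and the sample size uses one average edema value. If that value is a mean of lines, there is one primary test and nothing is inflated. The measurement method is cited to a source that is not at hand, and that source may combine the lines. The article is also a condensed account, and score derivation and multiplicity rules are often left to a fuller document.

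Part of this stands. The article nowhere says that the distances will be tested separately or that any one would suffice, so inflation is possible but not established. The scope argument carries less weight. Which number is primary is protocol content, because the sample size cannot be read without it. The article does not leave the matter blank either: it lists three distances as primary and sets one unadjusted level for all tests.

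Two stronger readings are tempting, and the documents support neither.

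- A reader might infer that the false positive chance is more than double 5%. That needs separate tests, success on any one line and an inter-line correlation below about 0.79. None of these is stated. Lines measured on the same swollen side may well be strongly correlated.
- A reader might count day 7 as three further primary tests, since that visit is listed under the primary outcome. The Abstract fixes 48 h as the primary time and the sample size uses the same time, so the listing reads as a measurement schedule.

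**Conclusion.** The point holds in a conditional form. The primary quantity is not defined: three distances are listed as primary, 5% applies to all tests, and the planning figure belongs to no identified line or combination.

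If each distance is tested at 5% at 48 h and any one counts, the false positive chance is about 7% (correlation 0.95) to 14% (independence) instead of 5%. This range assumes two-sided tests and one common correlation among the three lines. The size of that correlation is an assumption, since the article gives none. If the lines are combined into one value, there is no inflation. Even then the text needs correcting, because it does not say so and the scale of the planning figures remains unknown.

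**What to change.** State one primary quantity before any unblinded result is seen. Possible wording: *The primary endpoint is the mean of the three facial distances on the operated side at 48 h, adjusted for the mean of the same three distances before that surgery, with one test at two-sided 5%.* Make the single lines and day 7 secondary. Confirm that the 105, 109 and 5 mm planning figures are on this scale; if they are not, redo the sample size on the scale that will be tested.

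The mean is an example. One named line or a sum would also settle the matter, provided that it is fixed in advance and is the quantity used in the sample size.

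The change costs one sentence and one check of the planning source. It needs no new data, because all three distances are already scheduled before surgery and at day 2. The downside is small: averaging dilutes an effect confined to one line, and reporting the single lines as secondary results would still show it.

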### Medication protocols in the preoperative period

Control Group: Dexamethasone 8 mg, 1 tablet administered 1 hour before surgery.

Experimental Group: Photobiomodulation applied intraorally and extraorally 1 hour before surgery (detailed in the "Photobiomodulation method" section).

Medication protocols in the postoperative period (both groups):

Amoxicillin 750 mg tablet, orally every 12 hours for 7 days.

Anti-inflammatory medication: Ketorolac 10 mg every 6 hours for 3 days.

Analgesic medication: Paracetamol 500 mg every 6 hours for 3 days to be taken in the occurrence of pain (number of tablets taken will be quantified as a secondary outcome).

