Individuals who experience any complications during the research period, such as allergic reactions to any of the materials used, an allergic reaction to Paracetamol®, or having taken any other drug not provided, those who, in any way, become unable to attend the appointments on the scheduled dates, relocate to a different city, or simply no longer wish to participate in the research will be excluded from the study but will not suffer any negative consequences in terms of treatment.

The data of all participants will be included in the statistical analysis, described, and discussed, along with any potential major and minor adverse effects.

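### Paracetamol is given for 3 days but tablets are counted at day 7; the counting window and the handling of other analgesics need to be reconciled

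*Protocol article*

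**What the plan says.** Three places in the Methods of the protocol article bear on this outcome.

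- **Medication protocols, postoperative part (both groups).** The analgesic is "Paracetamol 500 mg every 6 hours for 3 days to be taken in the occurrence of pain", and the same entry adds that the "number of tablets taken will be quantified as a secondary outcome". Scheduled ketorolac is also given for 3 days.
- **Study outcomes, tablets taken.** "The number of analgesic tablets taken at two and seven days will be counted". The instruction to patients is "All participants will take paracetamol and be instructed to take it every six hours only in the presence of pain", with no last day. On supply, "each participant will be provided a paracetamol tablet" at the start of the study, which leaves the quantity unclear. On checking, "the patients will be asked to bring the medication blister pack to the appointment to check how it is being used".
- **Experimental design, text after Table 2.** The reasons for exclusion during the study include "or having taken any other drug not provided". The paragraph directly after it says that the data of every participant enter the statistical analysis.

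**The concern.** The medication section and the outcome section can be read as defining two different quantities under one name: the total of a 3-day course, or use over 7 days. A reader of the results could not tell which was reported.

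The exclusion rule adds to this. Both pain-relieving drugs in the stated regimen, ketorolac and paracetamol, end after 3 days, while pain is still scored at day 7. A patient with pain on days 4 to 7 who keeps to the 3-day rule adds nothing to the count. One who takes another analgesic meets a listed ground for exclusion. Needing another analgesic is closely related to the outcomes under study, so removing data for that reason is undesirable whatever its direction.

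**Working it through.** The plan states no figure for this outcome, so there is none to reproduce. The check is schedule arithmetic followed by a comparison of the passages.

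**Inputs.** Interval of 6 hours and course of 3 days (medication section); counts at two and seven days (Study outcomes); 30 patients with two surgeries each (Sample size calculation, Randomization). Assumption: one tablet per intake, since the article does not state the number.

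**Ceilings.** Maximum tablets = hours allowed / 6.

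| Window | 3-day limit governs | Open instruction governs |
|---|---|---|
| By day 2 | 48/6 = 8 | 48/6 = 8 |
| By day 3 | 72/6 = 12 | 72/6 = 12 |
| By day 7 | 12 (nothing added after day 3) | 168/6 = 28 |
| Possible increase after day 2 | 12 − 8 = 4 | 28 − 8 = 20 |

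Under the 3-day limit, the day-7 count covers 72 of 168 hours: 72/168 = 43%. All of the possible increase over day 2 falls on day 3. The day-2 ceiling is the same under both readings.

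**Use of a non-provided analgesic.** Two branches follow from the text after Table 2.

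1. *Exclusion is applied and the data are dropped.* Each patient contributes one surgery to each treatment, so the loss is a within-patient pair: 1 of 30, or 3.3% of the pairs per patient.
2. *The data are kept, as the next paragraph says.* The outcome counts paracetamol, and the described check is of the blister pack. The article describes no count of other analgesics, so the patient's extra use does not appear in the outcome.

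In neither branch does the stated outcome capture that use.

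**The case against.** The strongest reply is that the two sections are compatible. The medication entry attaches the outcome to the 3-day course itself. Days 2 and 7 are the common follow-up visits, and a 3-day course is unfinished at day 2, so day 7 is the first visit at which the completed count can be read from the pack. On this reading there is an interim count and a course total. This stands: a course total read at day 7 is a valid outcome, and the protocol nowhere claims to measure analgesic need over 7 days. A reader might infer that the day-7 count fails at its purpose; the document does not support that. What remains is that the outcome section gives no last day, so the compatible reading has to be supplied by the reader.

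A reader might also infer that the heaviest users are selectively lost and that the treatments would therefore look more alike than they are. The text does not show this, for four reasons:

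- The paragraph after the exclusion list says that all data will be analysed, so loss is possible but not settled.
- Nothing shows that those who take another drug after day 3 are the heaviest paracetamol users.
- In a split-mouth design a dropped patient takes both treatments' data along, so the simple picture of one arm losing patients does not apply.
- Tablets are taken only for pain and alongside ketorolac, and the article gives neither expected consumption nor a rate of late pain. Whether the ceiling would often be reached is unknown.

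Late pain is also measured directly by the visual analog scale at day 7. Finally, a line for other analgesics may exist in the full protocol or the case report form. That is possible, but it would not remove the conflict between the exclusion rule and the statement that all data are analysed.

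**Conclusion.** The concern holds as a matter of reconciliation and of handling other analgesics. If the 3-day limit governs, the day-7 count is a 3-day course total of at most 12 tablets, at most 4 above the day-2 count, and says nothing about days 4 to 7. If the open instruction governs, the ceiling is 28. These figures assume one tablet per intake at the stated interval.

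The more useful part concerns non-provided drugs. As written, their use either may remove a patient's pair or goes uncounted, and the document contradicts itself on which applies.

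The issue is minor. For the tablet count, only the day-7 secondary outcome is affected; the day-2 ceiling is the same under either reading. The document does not allow the size or direction of any effect on the treatment comparison to be derived, and no bias towards or away from either treatment is claimed.

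**What to change.** 1. Reconcile the medication and outcome sections so that the counting window equals the period in which paracetamol is supplied. Name the outcome accordingly, per surgery, for example 0 to 48 h and 48 h to the end of supply. Which supply period applies is for the investigators to decide.
2. Record any non-supplied analgesic (yes/no and amount) as part of this outcome, for each surgery.
3. Resolve the two statements after Table 2 so that taking a non-supplied analgesic does not remove the patient's data from the analysis.

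The cost is protocol wording and one extra line on the visit form. The drawback is that the outcome may have to be described as covering less than 7 days.

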Do you have difficulty swallowing due to the surgery?

Do you have difficulty tasting food?

Can you chew on the operated side?

Do you have difficulty sleeping due to the surgery?

Did you have difficulty speaking due to the surgery?

Has your appearance changed due to the surgery?

Do you experience nausea due to the surgery?

Dysphagia—The assessment of dysphagia will be conducted two and seven days after surgery through questions [27] and classification on a numerical scale: (0) total absence of dysphagia; (1) dysphagia for solid foods; (2) dysphagia for any liquid or solid food.

Assessment of the presence and intensity of hematoma/ecchymosis*—*The presence of hematoma/ecchymosis will be assessed by measuring the largest diameter of color changes on the skin of the cheek and submandibular region at two and seven days after surgery. The measurement will be performed by a previously calibrated evaluator, who will classify the occurrence of this event in four categories: (1) non-existent; (2) largest diameter less than 4 cm; (3) largest diameter between 4 and 10 cm; and (4) largest diameter greater than 10 cm, as described by Bjornsson et al. (2003) [30].

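### The hematoma outcome measures the largest bruise diameter but grades it only in four wide bands; analysing the diameter itself would keep information already collected.

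*Protocol article*

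**What the plan says.** In the protocol article, hematoma/ecchymosis comes under the heading "The secondary outcomes of the study will be" (Study outcomes). The method given is "measuring the largest diameter of color changes on the skin of the cheek and submandibular region at two and seven days after surgery". This is done by a calibrated evaluator "who will classify the occurrence of this event in four categories: (1) non-existent", followed by "2) largest diameter less than 4 cm; (3) largest diameter between 4 and 10 cm; and (4) largest diameter greater than 10 cm". The scale is taken from a cited published study.

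Statistical analyses summarises quantitative variables by mean and standard deviation and qualitative ones by frequency and percentage. It names no analysis specific to hematoma. The Sample size calculation section rests on edema alone, with 30 patients contributing one surgery to each arm.

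**The concern.** The evaluator has a length in hand, but the outcome defined is a grade with cut-points at 4 and 10 cm. Differences inside a band do not register. A bruise of 9 cm on one side and 4.5 cm on the other gives a tied pair, and so does 3.8 cm against 1.9 cm, although one bruise is half the size of the other in each case.

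In a split-mouth trial of 30 patients, pairs tied on the grade add nothing to a signed-rank comparison of treatments. At stake is the ability of this secondary outcome to show a difference in bruise size. If only the grade is entered on the form, the diameter cannot be recovered later.

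**Working it through.** **The plan's own figure.** There is none for hematoma: no expected diameter, no share of sides with a bruise and no target difference. The only computed figure, 30 surgeries per group, concerns edema. It is used here only as the number of pairs.

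**What needs no assumption.** Let g(d) be the grade: 1 if d = 0, 2 if 0 < d < 4, 3 if 4 ≤ d ≤ 10, 4 if d > 10 (cm).
- g(1) = g(3.8) = 2
- g(4.2) = g(9.5) = 3

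**Assumptions for the size of the loss** (none is in the article):
- Diameters are log-normal with log SD 0.6, and the control-side median runs from 2 to 8 cm.
- Within-patient correlation is 0.5, both for diameter and for the presence of a bruise.
- The treated-side diameter is 0.67 times the control-side diameter.
- Either no control side or 30% of control sides are free of bruising.
- There are 30 pairs and 1,500 runs per scenario. The test is a two-sided signed-rank test at 5%, applied to the diameter difference and then to the grade difference.

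Power, diameter against bands:

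| Control median | All sides bruised, treatment only shrinks | 30% unbruised, treatment only shrinks | 30% unbruised, treatment shrinks and adds 20 points of bruise-free sides |
|---|---|---|---|
| 2 cm | 0.91 v 0.15 | 0.42 v 0.08 | 0.85 v 0.56 |
| 3 cm | 0.91 v 0.53 | 0.42 v 0.15 | 0.85 v 0.68 |
| 4 cm | 0.91 v 0.69 | 0.42 v 0.20 | 0.83 v 0.70 |
| 6 cm | 0.89 v 0.80 | 0.41 v 0.22 | 0.83 v 0.73 |
| 8 cm | 0.90 v 0.82 | 0.43 v 0.19 | 0.83 v 0.73 |

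With every control side bruised and 20 points of prevention added, the 3 cm case gives 0.99 v 0.94, and the 6 and 8 cm cases give 0.99 v 0.99.

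**Why the loss varies.** The share of bruises below 4 cm is Φ(ln(4/m)/0.6) for median m.
- m = 2: the control share is Φ(0.693/0.6) = 0.876. The treated median is 0.67 × 2 = 1.34, giving Φ(1.094/0.6) = 0.966. A one-third reduction moves only 0.966 − 0.876 = 9 points of sides across a cut-point.
- m = 6: the control share is Φ(−0.405/0.6) = 0.250. The treated median is 4.02, giving Φ(−0.005/0.6) = 0.497. The same reduction moves about 25 points across the 4 cm cut, and the share above 10 cm also falls, from 0.197 to 0.064.

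The bands work when bruises straddle a cut-point and fail when they sit inside a band.

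**Other assumptions.** With log SD 0.5, a 40% smaller diameter and 30% of sides unbruised (presence correlated within patient), power is 70% v 6% (2 cm), 69% v 22% (3 cm), 69% v 34% (4 cm), 68% v 37% (5 cm) and 68% v 35% (7 cm). If treatment also raises bruise-free sides from 30% to 50%, it is 95% v 55% (2 cm), 95% v 74% (3 cm), 94% v 84% (4 cm) and 94% v 86% (6 cm). The direction is the same throughout.

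**The case against.** The strongest reply is that this is a published ordinal scale, used for a secondary outcome on which no sample size rests, and that nothing in the article is contradicted. That stands, and it fixes the point as an improvement rather than an error. It is also true that the article does not say the diameter is discarded, and that it promises descriptive analyses of all measured variables. But the outcome as defined is the grade, and no use of the diameter is named.

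Three stronger readings are tempting, and the article supports none of them.
- *Most treatment differences would be lost.* This needs a diameter distribution and an effect size that the article does not give. The category for no bruise still registers prevention, and with large bruises on every side most of the power survives.
- *Most pairs would be tied.* Across the assumptions tried, the tied share ran from 31% to 91%, so this is not a property of the scale as such.
- *The top band is out of reach because 10 cm is nearly a whole facial distance.* The Sample size calculation section says "The average edema measurement was 105 mm in the control group and 109 mm in the experimental group", and 100/105 = 95% and 100/109 = 92%. But the section does not say which facial line these means refer to. The bruise region includes the submandibular area, so such a line is no upper limit. In the main simulation 0% to 35% of control sides exceeded 10 cm.

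The outcome title speaks of intensity although only presence and extent are graded. That is cosmetic, since the grading is defined explicitly.

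**Conclusion.** The concern holds as a low-severity point. The protocol article takes a continuous measurement and defines the outcome as four wide bands, and in no scenario did the bands have more power than the diameter.

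The size of the loss depends wholly on assumed bruise data. It is nil or slight where nearly all sides have large bruises, and moderate in most cases where treatment also prevents bruises. It reaches most of the power (0.91 to 0.15, or 0.42 to 0.08) where bruises are small and shrink without disappearing. All these figures assume log-normal diameters, a within-patient correlation of 0.5 and a signed-rank test for both versions of the outcome. The primary outcome is unaffected.

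**What to change.** Record the largest diameter in mm, with 0 if no color change is present, for each operated side at days 2 and 7. State that this diameter is the analysed hematoma variable, compared between treatments within patient by a rank-based paired test such as the Wilcoxon signed-rank test. Derive the four published categories from it and report them as a descriptive table by treatment and visit.

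The cost is one numeric field on the case report form and one sentence in the analysis section, because the measurement is already taken. The downside is that the main hematoma result is no longer on the cited scale, though the table keeps the comparison with earlier studies.
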